**Table 3: Temporal course of blood investigations:**

| Test/Timepoint  | Volume (ml)                | Scr   | 0     | 7     | 28    | 84    | 168 (+/- 14) | 12.1 ^ (168-350) | 7 ◇ | 28    | 84    | 168   | Total (ml) |
|-----------------|----------------------------|-------|-------|-------|-------|-------|--------------|-----------------------------|----------------|-------|-------|-------|------------|
| FBC             | 4                          | X     |       | X     |       | X     |              | X                           | X              |       | X     |       | 20-24      |
| BioChem         | 4                          | X     |       | X     |       | X     |              | X                           | X              |       | X     |       | 20-24      |
| HBV/HCV/β-HCG   | 4                          | X     |       |       |       |       |              |                             |                |       |       |       | 4          |
| HIV             | 4                          | X     |       |       |       |       |              |                             |                |       |       |       | 4          |
| CD4             | 4                          | X     | X     | X     | X     | X     | X            | X                           | X              | X     | X     | X     | 40-44      |
| Viral Load      | 8                          | X     | X     | X     | X     | X     | X            | X                           | X              | X     | X     | X     | 80-88      |
| HLA             | 4                          |       |       |       | X     |       |              |                             |                |       |       |       | 4          |
| Research Bloods | 20-30 (16-26 at screening) | X     | X     | X     | X     | X     | X            |                             | X              | X     | X     | X     | 216-326    |
| TOTAL           | –                          | 44-54 | 32-42 | 40-50 | 36-46 | 40-50 | 32-42        | 0-20                        | 40-50          | 32-42 | 40-50 | 32-42 | 364-484    |

◇ Note that the days from this point on are shown as days after the second vaccination

^ FBC, Biochemistry, CD4 and VL will be repeated for exclusion criteria evaluation if a subject has been for their 6 month visit but was not vaccinated because the 6 month visit was prior to the second vaccination amendment.

### Definitions

The following definitions/clarifications outline the blood investigations that will be performed:

**Haematology\*** – full blood count (FBC) including platelet count

**Biochemistry\*** – urea, creatinine, albumin, ALT, alkaline phosphatase, potassium, sodium, total bilirubin

**Diagnostic serology\*** – hepatitis B surface antigen, hepatitis B surface antibody, hepatitis B core antibody and hepatitis C serology (IgG)

**Pregnancy test\*** – β-HCG (for women only)

**Exploratory immunology\*\*** – Ex-vivo Elispot assays for interferon-gamma

**Specific to HIV\*\*** – CD4 count, HIV serology and viral load.

\* Assays will be carried out at BIO 24 Laboratory

\*\* Assays will be carried out at CHU, Dakar, using standard procedures

Of the 20-30 ml blood taken for immunological assays, half will be required for immediate use, the other half will be stored as future research source.

In addition:

- Plasma and cells will be stored separately.
- Samples will be stored for up to 15 years.
- Plasma will be frozen down and stored for possible future use.

**Study Visits:****Study Day 0 (Day of vaccination)**

- An interim history will be taken and if considered necessary a physical examination emphasizing any acute complaints will be performed.
- A  $\beta$ -HCG urine test will be performed for female volunteers. Females will not undergo injection until the test is completed and reported as negative.
- Approximately 32-42 ml of blood will be collected for CD4 count, viral load and “exploratory immunology” tests.
- The vaccine candidate will be administered intradermally into the skin over the deltoid muscle of the appropriate arm. The injection site will be covered with a sterile dressing that will be removed at the one-hour observation.
- Vital signs will be checked at 30 minutes (+/- 5 mins) and 1hour (+/-10min) post injection.
- The injection site will be inspected at 1 hour (+/-10min) and the largest diameter of any hardness or redness as well as the degree of pain will be documented into the CRF. An assessment for possible systemic AE's will be carried out.
- It will be explained to the subject that there will be an active follow up for the first week, which will be at CRRCF-Fann by the trial nurse and/or clinician. The details of the visits (i.e. temperature, adverse event monitoring etc.) will also be described.
- A photograph of the vaccination site will be taken. The subject will only be identifiable by a unique study number.

**Contraindications to Vaccination**

The following adverse events constitute contraindications to administration of vaccine at that point in time; if any one of these adverse events occurs at the time scheduled for vaccination, the subject may be vaccinated at a later date, or withdrawn at the discretion of the investigator. The subject must be followed until resolution of the event as with any adverse event.

- Acute disease at the time of vaccination. (Acute disease is defined as the presence of a moderate or severe illness with or without fever.) All vaccines can be administered to persons with a minor illness such as diarrhoea, mild upper respiratory infection with or without low-grade febrile illness, i.e., temperature of  $<37.5^{\circ}\text{C}$ ).
- Temperature of  $\geq 37.5^{\circ}\text{C}$  at the time of vaccination

**Days 1–6 post vaccination (+/- 0 day)**

- An interim history will be taken and, if considered necessary a physical examination emphasizing any acute complaints will be performed. Vital signs will be checked and documented
- The injection site will be inspected and the largest diameter of any hardness or redness present, as well as the degree of pain reported for the time of the visit will be documented into the CRF.
- Solicited adverse events (local and general) that may have occurred since the vaccination will be documented in the CRF.

**Day 7 (+ 1 day)**

- An interim history will be taken and, if considered necessary a physical examination emphasizing any acute complaints will be performed. Vital signs will be checked and documented
- The injection site will be inspected and the largest diameter of any hardness or redness present, as well as the degree of pain reported for the time of the visit will be documented into the CRF.
- Solicited adverse events (local and general) that may have occurred since the vaccination will be documented in the CRF.
- Approximately 40-50 ml of blood will be collected for haematology, biochemistry, viral load, CD4 cell count and exploratory immunology.
- A photograph of the vaccination site will be taken. The subject will only be identifiable by a unique study number.

**Subsequent follow-up visits**

Volunteers will be reviewed at 28 (+/- 4 days), 84 (+/- 7 days) and 168 days (+/- 14 days) after vaccination.

- An interim history will be taken and, if considered necessary a physical examination emphasizing any acute complaints will be performed.
- Vital signs will be checked and documented
- The injection site will be inspected and the largest diameter of any hardness or redness present, as well as the degree of pain reported for the time of the visit will be documented into the CRF.
- Solicited adverse events (local and general) that may have occurred since the volunteer was seen on day 7 post vaccination will be documented in the CRF
- Approximately 32-42 ml of blood will be collected for exploratory immunology, viral load and CD4 cell count on day 28, 84 and 168. On day 84 only, haematology and biochemistry will also be performed; therefore, the blood volume will be 40-50 ml.
- On Day 28, HLA typing will be done; therefore, the total blood volume will be 36-46.

**Booster vaccination:**

- For Group 1, if Day 168 visit is before Protocol 2.0 amendment, the second vaccination will be given between days 168-350 (visit 12.1). However, before the subject receives the second vaccination, all inclusion and exclusion criteria except number 5 (Prior receipt of a recombinant MVA or Fowlpox vaccine) will be reviewed to check if the subject is still eligible to receive the vaccine. At this additional visit, 20 ml of blood will be collected to perform FBC, Biochemistry, CD4 and VL tests. Urinalysis, to exclude glycosuria and significant proteinuria will be performed. If any exclusion criterion are met except number 5, the subject will not be revaccinated.
- For Group 2, the second vaccination will be given at Day 168 (+/- 14 days)
- A photograph of the vaccination site will be taken after revaccination. The subject will only be identifiable by a unique study number.

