### **Secondary:**

To assess the immune responses induced by two vaccinations with MVA85A in healthy subjects who are infected with HIV, including the boosting affect of second MVA85A vaccination

To compare the immune response between subjects who are and who are not on ARVs after vaccination with MVA85A

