#### **Secondary:**

To assess the effect of vaccination with MVA85A in healthy subjects who are infected with HIV on the immune response to antigen 85A (the antigen in the vaccine) and to ESAT-6 and CFP-10 (markers of TB infection).

The effect of a booster vaccination at six months will also be assessed.

A comparison between the immune responses by HIV-infected people who are not and are on ARVs will also be done.

The specific endpoints for immunogenicity will be markers of cell-mediated immunity as outlined below:

- Ex-vivo Elispot assay for interferon gamma: (exploratory immunology)

In all previous TB vaccine trials this has been the main immunological readout. However, there are as yet no validated cellular immunological assays and no perfect correlate of protection has been identified for TB. There is therefore ongoing work in the laboratory to develop other cellular assays including flow cytometry tests.

In view of this, other immunological assays may include:

- ex-vivo elispot assays for interleukin-2 and tumour necrosis factor alpha
- cultured elispot
- T cell proliferation
- whole blood assay for interferon-gamma
- T cell depletion assays
- cytokine detection using ELISA/LUMINEX or
- intracellular staining and FACScan analysis will be performed at the discretion of the investigators. (This also includes gene expression studies.)
- any other immunological assays that are developed during the timeline of the trial

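### Visit 12.1 gives the second vaccination without a research blood sample, so the latest pre-boost ELISPOT for subjects boosted there may be up to about six months old

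*Protocol*

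**What the plan says.** The second vaccination was added by amendment. For Group 1 subjects who had already passed their six-month visit, the Booster vaccination section states that "the second vaccination will be given between days 168-350 (visit 12.1"). On the bloods for that visit it says: "At this additional visit, 20 ml of blood will be collected to perform FBC, Biochemistry, CD4 and VL tests". The footnote to Table 3 gives the purpose: "FBC, Biochemistry, CD4 and VL will be repeated for exclusion criteria evaluation". The Research Bloods row of Table 3 is blank in the 12.1 column, whose total is 0-20 ml. Table 2 marks vaccination at this visit.

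The last immunology sample before it comes from the routine follow-up: "Approximately 32-42 ml of blood will be collected for exploratory immunology, viral load and CD4 cell count on day 28, 84 and 168". The Day 168 visit has a window of 14 days either side. The next immunology sample is at day 7 after the second vaccination. Group 2 is to be boosted at the Day 168 visit itself, where Table 3 does mark Research Bloods.

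Section 2 lists the immune response to two vaccinations as a secondary objective, "including the boosting affect of second MVA85A vaccination". Section 7 repeats it as an outcome: "The effect of a booster vaccination at six months will also be assessed". Section 10 states that the analysis is descriptive only.

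**The concern.** Three visits can carry a vaccination: Day 0, Day 168 and visit 12.1. Only visit 12.1 has no immunology sample. A subject boosted there goes from the Day 168 sample to day 7 after dose 2 with nothing between.

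If the response to dose 1 goes on falling after Day 168, that sample overstates the level at the time of the boost, and a rise measured from it is too small. If mycobacterial exposure raises the response in the interval, the rise is too large. The data cannot show which has happened. No analysis plan can recover a sample that was not drawn, so this is not something left to the SAP. The Rationale section offers the second dose as one of two ways to improve immunogenicity in this population, so the boosting result is meant to be used.

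**Working it through.** **1. Is there room for a research sample in the 20 ml?** Volumes from Table 3: FBC 4, biochemistry 4, CD4 4, viral load 8.

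4 + 4 + 4 + 8 = 20 ml, which reproduces the stated 20 ml exactly. A research draw is 20-30 ml after screening. Nothing is left for it.

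**2. How old is the latest pre-boost ELISPOT?** Age = day of second vaccination minus day of the last research blood.

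| Day 168 visit held on | Boost on Day 350 | Age of sample |
|---|---|---|
| Day 154 (early limit) | 350 - 154 | 196 days |
| Day 168 (nominal) | 350 - 168 | 182 days |
| Day 182 (late limit) | 350 - 182 | 168 days |

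These are maxima. A boost given soon after the Day 168 visit leaves a gap near 0. For subjects boosted at the Day 168 visit the gap is 0, assuming that the blood is taken before the injection.

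**3. What could the gap do to a fold-rise?** The protocol gives no waning rate, so this step rests on assumption. Suppose the response halves every *h* days after Day 168 and the gap is *g* days. The level at the boost is then the Day 168 level times 2^(-g/h), and a fold-rise taken from Day 168 is too small by the factor 2^(g/h).

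| Assumed half-life | g = 0 | g = 182 days |
|---|---|---|
| 90 days | 1.0 | 2^(182/90) = 4.06 |
| 180 days | 1.0 | 2^(182/180) = 2.02 |
| 365 days | 1.0 | 2^(182/365) = 1.41 |

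The model has no floor. A plateau after Day 168 would bring every factor towards 1.0, and a rise through exposure would put it below 1.0.

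**4. How many subjects?** Group 1 has 12. Visit 12.1 applies only to those whose six-month visit came before the amendment. Their number is not given, and under the Rationale section they may decline the second dose. The count is at most 12.

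**5. Blood volume with the draw added.** Visit 12.1 becomes 20 + (20 to 30) = 40-50 ml. The column totals of Table 3 as printed sum to 368-488 ml, so the maximum becomes 488 + 30 = 518 ml.

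**6. A separate slip in the same table.** Research Bloods as ticked come to (16 to 26) + 9 x (20 to 30) = 196-296 ml. The printed row total is 216-326 ml, one 20-30 ml draw more. The printed grand total is 364-484 ml against the column sum of 368-488 ml.

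**The case against.** The best defence is that the protocol nowhere defines the booster effect as a rise from a sample taken at the boost. Samples fall on days 7, 28, 84 and 168 after each dose, so levels after dose 2 can be set beside levels at matched times after dose 1, or beside Day 0. Safety is the primary objective, the analysis is descriptive, and no test, decision rule or sample size depends on the missing sample. All of this stands. One useful contrast is weakened; the objective is not lost.

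Several stronger conclusions are tempting, and the documents do not support them:

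- *The boost is understated about fourfold.* That figure needs the shortest assumed half-life, the longest nominal gap and no floor. The protocol describes pre-existing mycobacterial immunity from BCG or exposure, which could supply a floor, and exposure could reverse the direction.
- *Most or all of Group 1 is affected.* The protocol does not say how many are.
- *The comparison by ARV status is spoiled, and the draw would repair it.* The age of the pre-boost sample does differ between the groups. But they are not randomised and also differ in dose interval, which a sample at 12.1 would not change. The stated objective compares responses after vaccination, not boosting specifically. That only Group 1 is affected also rests on the Booster vaccination section: the Rationale gives the ARV arm an interval of about 6 to 12 months, and the visit 12.1 footnote names no group. Those passages need reconciling.
- *The surplus in the Research Bloods total shows that a draw at 12.1 was intended.* The blank cell, the column total, the footnote and the visit text all exclude one.

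**Conclusion.** The sampling gap is real. Subjects boosted at visit 12.1 have no ELISPOT at the time of the second injection, and their latest earlier one is between about 0 and 182 days old, or 196 at the window limit. Change in the dose-1 response over that time cannot be told apart from the effect of dose 2, in either direction. The size is unknown. The factor of 1.0 to 4.1 is an illustration under stated assumptions, not an estimate. Treating Day 168 as the reference is also an inference: it is simply the latest sample these subjects have.

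The gap affects ELISPOT only, since CD4 and viral load are measured again at 12.1. It limits a descriptive secondary objective in an unstated number of subjects, at most 12. A reader might infer that the trial cannot describe boosting in Group 1 or that its main purpose is at risk; neither follows. This is a cheap improvement worth making, not a condition for the trial to be sound.

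**What to change.** - In Table 3, mark Research Bloods (20-30 ml, before injection) at visit 12.1. In the Booster vaccination section, change 20 ml to 40-50 ml and name exploratory immunology among the tests.
- State that the dose-2 reference is the last sample before the second injection.
- Say where the sample is taken if the eligibility bloods and the injection fall on different days. The protocol does not establish that they coincide, and screening results take a week. In that case, take the research sample at the injection attendance.
- Keep subjects already boosted without the sample in the summary, using Day 168. Flag them, show each subject's gap, and show the results without them as well. Simply leaving them out could empty Group 1.

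Cost: a short amendment, 20-30 ml more blood per affected subject (maximum column total 518 ml), at most 12 extra ELISPOT runs, and possibly a second venepuncture where the two attendances differ.

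Separately, correct the Table 3 totals (196-296 ml for Research Bloods as now ticked, 368-488 ml overall) and recompute them once the new draw is added. The 652.5 ml in the Potential risks section agrees with neither total and should be reconciled at the same time.

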### **Exclusion Criteria**

- Any clinically significant abnormal finding on screening biochemistry or haematology blood tests or on urinalysis
- Previous history of TB disease and/or treatment
- Any AIDS defining illness
- CXR showing TB or evidence of other active infection
- Prior receipt of a recombinant MVA or Fowlpox vaccine
- Use of any investigational or non-registered drug, live vaccine or medical device other than the study vaccine within 30 days preceding dosing of study vaccine, or planned use during the study period
- Administration of chronic (defined as more than 14 days) immunosuppressive drugs or other immune modifying drugs within six months of vaccination. (For corticosteroids, this will mean prednisolone, or equivalent,  $\geq 0.5$  mg/kg/day. Inhaled and topical steroids are allowed.)
- History of allergic disease or reactions likely to be exacerbated by any component of the vaccine, e.g. egg products
- Presence of any underlying disease that compromises the diagnosis and evaluation of response to the vaccine (including evidence of cardiovascular disease, history of cancer (except basal cell carcinoma of the skin and cervical carcinoma in situ), history of insulin requiring diabetes mellitus, any ongoing chronic illness requiring ongoing specialist supervision (e.g., gastrointestinal), and chronic or active neurological disease)

- History of  $\geq 2$  hospitalisations for invasive bacterial infections (pneumonia, meningitis)
- Suspected or known current drug and/or alcohol abuse
- Seropositive for hepatitis B surface antigen (HBsAg) and/ or hepatitis C (antibodies to HCV)
- Evidence of serious psychiatric condition
- Any other on-going chronic illness requiring hospital specialist supervision
- Any confirmed or suspected immunosuppressive or immunodeficient condition, **other than** HIV infection, such as asplenia
- Evidence of hepatomegaly
- Administration of immunoglobulins and/or any blood products within the three months preceding the planned administration of the vaccine candidate
- Pregnant/lactating female and any female who is willing or intends to become pregnant during the study
- Any history of anaphylaxis in reaction to vaccination
- PI assessment of lack of willingness to participate and comply with all requirements of the protocol, or identification of any factor felt to significantly increase the participant's risk of suffering an adverse outcome

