**Events at screening:**

- A baseline medical history and physical examination will be performed
- Inclusion and exclusion criteria will be checked using a tabulated format
- Vital signs will be checked
- Subjects will be counselled by one of the investigators for Hepatitis B and Hepatitis C testing
- Blood will be drawn for HIV, HBV and HCV testing, haematology, biochemistry, viral load and CD4 cell count, typing for HLA variants, other genetic variants that may be relevant to the immune response to vaccines, and exploratory immunological assays. A serum  $\beta$ HCG test will be done on women to test for pregnancy.
- Urinalysis, to exclude glycosuria and significant proteinuria will be performed
- A chest-x ray will be performed if there is not an available film that has been performed in the last 3 months.
- 1 week after screening, volunteers will attend to obtain their results.

All documents and procedures will be in French, having been translated and backtranslated from English. Wolof translators will be present when necessary.

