**Table 2: Illustration of sequential events (screening and subsequent follow-up):**

| Visit number              | 1         | 2              | 3–8 | 9   | 10  | 11  | 12             | 12.1 ^ | 13–18            | 19  | 20  | 21  | 22  |
|---------------------------|-----------|----------------|-----|-----|-----|-----|----------------|-------------------|------------------|-----|-----|-----|-----|
| Day                       | Screening | 0              | 1–6 | 7   | 28  | 84  | 168
(+/-14) | 168-350           | 1–6 ◇ | 7   | 28  | 84  | 168 |
| Medical history           | √         | (√)            | (√) | (√) | (√) | (√) | (√)            | (√)               | (√)              | (√) | (√) | (√) | (√) |
| Physical examination      | √         | (√)            | (√) | (√) | (√) | (√) | (√)            | (√)               | (√)              | (√) | (√) | (√) | (√) |
| Vital signs °  | √         | √              | √   | √   | √   | √   | √              | √                 | √                | √   | √   | √   | √   |
| Urinalysis                | √         | √ † |     |     |     |     | √ † | √ †    |                  |     |     |     |     |
| Chest x-ray #  | √         |                |     |     |     |     |                |                   |                  |     |     |     |     |
| Venepuncture              | √*        | √*             |     | √*  | √*  | √*  | √*             | √*                |                  | √*  | √*  | √*  | √*  |
| Vaccination               |           | √              |     |     |     |     | √              | √                 |                  |     |     |     |     |
| Injection site inspection |           | √              | √   | √   | √   | √   | √              | √                 | √                | √   | √   | √   | √   |
| Adverse events documented |           | √              | √   | √   | √   | √   | √              | √                 | √                | √   | √   | √   | √   |

(√) If considered necessary (emphasizing any acute complaints)

^ Visit 12.1 is only required if a subject has been for their 6 month visit but was not revaccinated because the 6 month visit was prior to the second vaccination amendment

° Temperature (°C), blood pressure (mmHg), pulse rate (beats/minute)

† Women only for pregnancy test

# Performed if no available CXR within the last 3 months

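### Table 2 limits visit 12.1 urinalysis to a pregnancy test in women, but the booster text requires a glucose and protein check in every subject before re-dosing

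*Protocol*

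**What the plan says.** Visit 12.1 is a catch-up visit in Protocol section 5. It exists only for subjects whose six-month visit took place before the amendment that introduced a second vaccination. Under Booster vaccination, before such a subject is re-dosed, "all inclusion and exclusion criteria except number 5 (Prior receipt of a recombinant MVA or Fowlpox vaccine) will be reviewed". The same bullet orders repeat bloods and a urine test and states the consequence: "Urinalysis, to exclude glycosuria and significant proteinuria will be performed. If any exclusion criterion are met except number 5", there is no second dose. The urine test is ordered for glycosuria and significant proteinuria, in the same terms as at screening, and is not restricted to women.

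The first item in the Exclusion Criteria is "Any clinically significant abnormal finding on screening biochemistry or haematology blood tests or on urinalysis". A later item is "Evidence of hepatomegaly".

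Table 2 has four marks in its urinalysis row. Screening has a plain tick. Day 0, Day 168 and visit 12.1 have a tick with a dagger, and the dagger is explained as "Women only for pregnancy test". In the physical examination row, screening has a plain tick. Every later column, including 12.1, has a bracketed tick, which leaves the examination to the investigator's judgement with acute complaints in mind.

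**The concern.** The second dose depends on the re-check: meeting any exclusion criterion other than number 5 bars it. A site can apply that bar only if the tests behind it are done, and Table 2 is the natural visit checklist. A site working from it at 12.1 would test women's urine for pregnancy and take no urine from men. The urinalysis part of the first exclusion criterion would then go unassessed before a second injection of an investigational vaccine, in a trial whose primary objective is safety. What is at stake is a pre-dosing check. No estimate, comparison or endpoint definition depends on it.

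**Working it through.** The protocol gives no figure to reproduce here. The check sets the four urinalysis marks in Table 2 beside the text for the same visits.

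| Visit | Table 2 mark | What the text asks for | Result |
|---|---|---|---|
| Screening | plain tick | Events at screening: urinalysis for glucose and protein | agrees |
| Day 0 | tick with dagger | Study Day 0: urine pregnancy test, women only | agrees |
| Day 168 | tick with dagger | Visit text names no urine test; Reporting of Pregnancy wants a urine pregnancy test on the vaccination day | no conflict |
| 12.1 | tick with dagger | Booster vaccination: urinalysis for glucose and protein, no limit by sex | conflicts |

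One cell of four conflicts. The table itself uses two different marks, plain for the full urinalysis and dagger for the pregnancy test, and it puts 12.1 in the second class.

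**Could the dagger be read another way?** Suppose it meant urinalysis for everyone, with a pregnancy test added for women. Visit 12.1 would then agree with the text. But Day 0 and Day 168 would call for a full urinalysis that no visit text mentions, so two cells of four would lack support instead of one. The pregnancy-only reading fits the document better, and under either reading the row needs correcting.

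**Does another test at 12.1 fill the gap?** The text and Table 3 list FBC, biochemistry, CD4 and viral load. Definitions gives the biochemistry panel as urea and creatinine (2), sodium and potassium (2), ALT and alkaline phosphatase (2), albumin (1) and total bilirubin (1): 2 + 2 + 2 + 1 + 1 = 8 analytes. None is glucose. Serum albumin and creatinine bear only indirectly on urinary protein.

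**Was the rest of the schedule aligned with the re-check?** Table 3 volumes at 12.1 are FBC 4 + biochemistry 4 + CD4 4 + viral load 8 = 20 ml, which equals the 20 ml in the booster text. The Table 3 footnote also ties these bloods to the evaluation of exclusion criteria. Table 3 follows the re-check; the urinalysis row of Table 2 does not.

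**How many subjects?** Group 1 is planned at 12 of 24. Only those who passed Day 168 before the amendment, and who accept a second dose, reach 12.1. The number is not stated, so the range is 0 to 12, at most 12/24 = 50% of the trial.

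**The case against.** The strongest reply is that the text governs. Section 5 introduces Table 2 as an illustration and says that the visit descriptions give the detail. The paragraph written for this one visit orders the test in plain terms, just before the rule that bars dosing. Table 2 is also shorthand elsewhere: it brackets medical history at every visit after screening, although most visit descriptions require an interim history. A site that relied on the table alone would already be departing from the text. This stands as far as it goes. The requirement exists, the correct reading can be found, and harm needs a site to follow the table against the text. It does not remove the contradiction between two current parts of the protocol, at a visit where the result decides whether a dose is given.

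It can also be said that the first exclusion criterion concerns screening results. That does not help, because the booster text orders the urinalysis at 12.1 in its own right.

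On the examination, a reader might infer a second contradiction: hepatomegaly must be re-checked, yet the examination is optional. The documents do not support that. The criterion must be reviewed, and the bracketed tick lets the investigator examine whenever it is considered necessary, which can include that review. Screening does require it outright ("A baseline medical history and physical examination will be performed"), but the booster text names no examination at 12.1, so there is nothing for the table to contradict. What is left is a point that could be stated more clearly.

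**Conclusion.** The point holds for urinalysis at visit 12.1. Table 2 contradicts the Booster vaccination text in one cell, and followed literally it would omit the glucose and protein check in up to 12 Group 1 subjects, with no urine test at all in the men. This assumes that the dagger means what its footnote says and that some site staff work from the schedule. It is a low-priority correction: the text is already right, the safety gain is small, and no endpoint or analysis is touched.

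Three stronger readings should not be drawn:

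- A reader might infer that the protocol fails to require the urine check. It does require it; only the schedule is wrong.
- A reader might infer that the pregnancy test is missing at 12.1 because the booster paragraph does not name it. Table 2 schedules it, and Reporting of Pregnancy requires it on vaccination day.
- A reader might infer that the last mandatory examination, at screening, is too old by the time of 12.1. The 90-day limit governs how long before vaccination the screening visit may take place. The protocol sets no maximum age for an examination before the second dose, and discretionary examinations are available at every visit in between.

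**What to change.** In Table 2, urinalysis row, visit 12.1, replace the dagger mark with one whose footnote says that urinalysis for glucose and protein is done in all subjects, with a urine pregnancy test in addition for women. Leave the Day 0 and Day 168 marks as they are.

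Optionally, add a short note to the Booster vaccination text that a physical examination is done at 12.1 where it is needed to re-check for hepatomegaly. This is a clarification only.

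The cost is one table cell and its footnote. In practice it means a urine test that the text already requires, for at most 12 subjects at a visit they attend anyway, with no added blood test or film.
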